### Objectives and hypotheses

This study will investigate 1) near-transfer gains associated with working memory and processing speed training in schizophrenia patients (that is, gains in the working memory or processing speed domains, respectively); 2) far-transfer gains associated with working memory and processing speed training in schizophrenia patients (that is, gains in other neurocognitive domains, primarily fluid intelligence, and gains in social cognition); and 3) real-world gains associated with working memory and processing speed training in schizophrenia patients (that is, gains in daily functioning). In addition, exploratory analyses will examine the effect of individual difference variables (that is, sleep quality and intrinsic motivation) on training-related gains. The primary outcome measures are as follows: working memory, processing speed, and fluid intelligence.

The corresponding hypotheses are as follows: 1) post-training performance in working memory and processing speed will improve in the working memory training group and processing speed training group, respectively, relative to the no-training control group (that is, both training groups will show near transfer in their own domain); 2) both working memory and processing speed training will lead to more generalized improvements in other neurocognitive domains, particularly fluid intelligence, compared to the no-training control group, as well as enhancements in social cognition relative to the no-training control group; and 3) both working memory and processing speed training will lead to more improvements in daily functioning compared to the no-training control group. Given the current paucity of research comparing the gains associated with specific training programs, no hypotheses are made with regards to which training group (that is, working memory or processing speed) will show greater improvements in neurocognition, social cognition, or daily functioning. Rather, comparisons between training groups will be exploratory in nature.

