### Recruitment process and study population

Up to 81 schizophrenia patients will be recruited. This is based on a power calculation with an alpha-level of .05, power of .80, and an effect size of *d* = .70, with the effect size derived from a recent study examining a more specific cognitive remediation program (that is, auditory working memory training) in schizophrenia [58]. Importantly, this sample size accounts for dropout rates of up to 10 %, based on previous cognitive training studies [82]. Recruitment status is currently pending, with plans to start in January 2016. Patients will be recruited through outpatient clinics at Foothills Medical Centre and through community support programs in Calgary, Alberta, after receiving appropriate permissions to enter the clinics and discuss the study. Participants will also be recruited through an existing participant database at the University of Calgary. Inclusion criteria for all participants will be as follows: (1) a diagnosis of schizophrenia or schizoaffective disorder, assessed with the Structured Clinical Interview for DSM-5 (SCID-5) interview; (2) age 18 to 65 years; (3) no uncorrected visual impairment, including color blindness, determined by self-report; (4) no uncorrected hearing impairment, determined by self-report; and (5) able to provide informed consent, determined by the clinical experience of the researchers. Exclusion criteria will be as follows: (1) meeting Diagnostic and Statistical Manual - 5^th^ edition (DSM-5) diagnostic criteria for a current major depressive episode, manic episode, or hypomanic episode, assessed with the SCID-5 interview; (2) use of electroconvulsive therapy (ECT) or transcranial magnetic stimulation therapy (TMS) within the past month, determined by self-report; (3) recent (that is, within past 3 months) history of substance-use disorder (excluding nicotine, cannabis, or caffeine), assessed with the SCID-5 interview; (4) diagnosed with a medical condition known to affect cognition (for example, endocrine disease or uncontrolled diabetes), determined by self-report; and (5) score less than 70 on the Wechsler Abbreviated Scale of Intelligence (WASI-II). In addition, only individuals who have access to the internet on a home computer will be eligible to participate in the study.

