**Fig. 1 Fig1:**
[figure not shown]
Participant flow through study. This figure illustrates participant enrollment, allocation, and follow-up throughout the study

All participants who meet the inclusion criteria will be randomly assigned to one of three conditions: (1) a working memory-training condition (27 participants), (2) a processing speed-training condition (27 participants), or (3) a no-training control condition (27 participants). Participants in the two training conditions will be blind to the fact that there are multiple training groups and to which cognitive domain they have been assigned to (that is, no mention of “working memory” or “processing speed” will be made). Group assignment will be determined by a Microsoft Excel randomization generator (that is, computer-generated random numbers). The random allocation sequence will be generated by a trained research assistant. Randomization will be performed as complete randomization with a 1:1:1 allocation. The allocation sequence will be concealed in sealed envelopes until the end of the pre-training assessment. A trained research assistant will also assign participants to interventions. Participants who are randomly assigned to the no training control condition will be given the opportunity to access the cognitive training games after their post-assessments. All researchers administering pre- and post-assessments will be blind to the group assignments of each participant.

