##### Intrinsic motivation inventory

Finally, brief self-report motivation questionnaires (that is, the Intrinsic Motivation Inventory) [103] will be provided to patients to complete prior to training, during training (that is, one time approximately half-way through training), and immediately post-training. This questionnaire will measure motivation, engagement, and self-regulation.

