### Statistical analysis

The following demographic variables at screening will be summarized: ethnicity, sex, age, and education. Between-group analyses of variance (ANOVAs) and chi square analyses will be used to examine any baseline differences between groups in demographics, individual characteristics (for example, sleep), cognition, and/or functioning. Any baseline differences will be corrected in all further analyses as appropriate.

Next, a three-group (working memory training, processing speed training, or no training) x time (pre-training or post-training) repeated measures ANOVA will be conducted to test for significant group differences in each domain of neurocognition (that is, memory, processing speed, executive functioning, and fluid intelligence) over time. Follow-up one-way repeated measures ANOVAs will be conducted as necessary to further examine the main effects of time. Follow-up independent *t*-tests will be conducted to examine differences in training- related gains between each training group and the no-training control group, based on the above-described *a priori* study objectives. Cohen’s *d* effect sizes will be reported. Notably, composite measures will be used where applicable (for example, a working memory composite, a processing speed composite).

Similarly, a group x time repeated measures ANOVA will be conducted to test for significant group differences in each social cognition task and each measure of daily functioning, with follow-up one-way repeated measures ANOVAs to follow-up on main effects of time and independent *t*-tests to examine group differences. Again, Cohen’s *d* effect sizes will be reported.

Finally, exploratory simple regression analyses will be conducted to examine potential moderating factors of training-related change. For any aspects of cognition and functioning that show significant training-related gains, regression analyses will be conducted using individual difference variables (for example, medication usage, sleep quality, duration of illness, intrinsic motivation) as the independent variable and change scores for each cognitive or functional domain as the dependent variable.

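### The planned one-predictor regressions of change scores cannot separate moderators of the training effect from general predictors of retest change

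*Protocol article*

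**What the plan says.** In the protocol article, Objectives and hypotheses sets the aim: "exploratory analyses will examine the effect of individual difference variables (that is, sleep quality and intrinsic motivation) on training-related gains". No model is given there.

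The Statistical analysis section supplies one. It says that "exploratory simple regression analyses will be conducted to examine potential moderating factors of training-related change". It then fixes four things:

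- **When it is run:** "For any aspects of cognition and functioning that show significant training-related gains, regression analyses will be conducted using individual difference variables".
- **Candidate variables, given as examples:** "medication usage, sleep quality, duration of illness, intrinsic motivation".
- **Model terms:** the variable enters "as the independent variable and change scores for each cognitive or functional domain as the dependent variable".
- **Form:** simple regression, that is, one predictor at a time.

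Neither arm nor an arm-by-variable product is named, and the section does not say whether controls are included. The Intrinsic motivation inventory section has motivation measured "prior to training, during training (that is, one time approximately half-way through training), and immediately post-training". The regression text does not say which of these values is used.

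**The concern.** A moderator changes the effect of training relative to no training. In a three-arm trial that means the slope of change on the variable differs between a trained arm and control. A regression with one predictor estimates a single slope and compares it with zero, not with the slope in another arm.

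The gap matters in this design because change without training is plausible. Alternate forms or item sets are described for Raven's matrices, the Cattell test and the Hinting Task, but not for the working memory and processing speed tests. Some practice gain on those tests can therefore be expected in every arm. A variable such as sleep or motivation that predicts practice gain could be significant with no bearing on who benefits from training.

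The trial has what is needed to tell the two apart: an untrained arm assessed before and after the same 10 weeks. The planned model does not use it as a comparison. What is at stake is the exploratory aim on sleep quality and motivation. As specified, the analysis would describe who changes, not for whom training works.

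**Working it through.** The plan states no figure for this analysis, so there is nothing to reproduce. The check asks how often the planned regression is significant when there is no moderation at all.

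**Inputs from the protocol article.** 27 patients per arm: "Up to 81 schizophrenia patients will be recruited" and "Randomization will be performed as complete randomization with a 1:1:1 allocation", with 27 listed for each condition. Training gain d = 0.70, the effect size in the sample size statement.

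**Assumptions.** The variable has the same within-arm correlation r with change in all three arms, so no moderation exists. The documents give no r; the range used is 0, .3, .4 and .5. Tests are two-sided at .05.

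**Simulation** (4,000 trials per setting, 27 per arm), percentage of trials with p < .05:

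| Analysis | r = 0 | r = .3 | r = .4 | r = .5 |
|---|---|---|---|---|
| Simple regression, all arms pooled | 4.9 | 75 | 94 | 99.6 |
| Simple regression, both trained arms | 5 | 60 | 86 | 98 |
| Simple regression, one trained arm | 5 | 33 | 55 | 78 |
| Arm × variable interaction, working memory arm against control | 4.8 | 5.0 | 5.2 | 4.8 |

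With 24 per arm (27 less about 10% dropout) the pooled figures are 68%, 92% and 99% at r = .3, .4 and .5.

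**Check by formula.** The chance of significance is approximately Φ(atanh(r)·√(n − 3) − 1.96).

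- One trained arm, n = 27, r = .3: 0.3095 × 4.899 − 1.96 = −0.444, giving 33%.
- Both trained arms, n = 54, r = .3: 0.3095 × 7.141 − 1.96 = 0.250, giving 60%.
- All arms, n = 81, r = .3: the training gain, unmodelled, adds 0.49 × (2/3)(1/3) = 0.109 to the variance. The correlation falls to .3/√1.109 = .285, and 0.293 × 8.832 − 1.96 = 0.628, giving 73.5%.
- At r = .4 the same steps give 55%, 86% and 94%.

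These agree with the simulation to within about 1.5 percentage points.

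**The opposite error.** Take slopes of +0.25 in both trained arms and −0.5 in control, per SD of the variable. The average slope across arms is (0.25 + 0.25 − 0.5)/3 = 0. The pooled regression is significant in 6.6% of trials although training benefit depends strongly on the variable. The interaction test is significant in 73% (one trained arm against control) or 85% (both trained arms against control).

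**Power of the interaction test.** For slopes of 0.5 in the trained arms and 0 in control, simulated power is 41% (one trained arm against control) or 53% (both against control). The large-sample formula gives slightly higher values. The standard error is √(1/27 + 1/27) = 0.272 or √(1/54 + 1/27) = 0.236, so Φ(0.5/0.272 − 1.96) = 45% and Φ(0.5/0.236 − 1.96) = 56%.

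**The case against.** The strongest reply is that the article calls the analysis exploratory and the factors only potential, and that no hypothesis or primary outcome depends on it. That stands and limits the severity. It does not remove the point: an exploratory label excuses imprecision, but here the model estimates a different quantity from the one named.

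Second, the percentages for the simple regression are its power to find a real predictor of change. They become errors only if the result is reported as moderation. That is correct, and it is why relabelling is an acceptable remedy.

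Third, the wording may mean that only trained patients are analysed. The article does not settle this. The rates are then lower (60% and 86%, or 33% and 55%), but there is still no control slope to compare with.

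Several stronger readings are tempting and are not supported:

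- *The analysis will mislabel predictors.* It can. If a variable is unrelated to change, the error rate is the nominal 5%.
- *Motivation measured during or after training will be used as a moderator.* The article lists the measurement times but does not say which value enters the regression; the pre-training value fits the text equally well. A later value would be a problem, since it follows randomization and could result from the gain.
- *Limiting the analysis to outcomes with significant gains causes the mislabelling.* It does not. It limits the number of tests. Its cost is selection, including skipping outcomes where opposite subgroup effects cancel on average.
- *The results would misdirect who is offered training.* The article gives these regressions no such role.

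**Conclusion.** The point holds as a mismatch between a stated purpose and a stated model. Because the article fixes the predictor, the outcome and the form of the regression, this is not a detail left to a fuller plan, and no other section repairs it.

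The size depends on an unknown correlation and on which arms are analysed. For r of .3 to .4, equal in every arm, and 27 per arm, a variable that moderates nothing is significant in between 33% (one trained arm, r = .3) and 94% (all arms, r = .4) of trials. Real moderation can also be missed when slopes in trained and control patients have opposite signs.

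Severity is low to moderate: the analysis is exploratory and no primary conclusion rests on it.

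**What to change.** For each variable, take the value obtained before randomization (for motivation, the pre-training questionnaire). In all three arms, fit the outcome on arm, variable and arm × variable. The outcome can remain the change score, or be the post score adjusted for the pre score; either allows the test. Report the interaction for each trained arm against control with its 95% confidence interval, as hypothesis-generating. Do this at least for the primary composites, whether or not the main effect is significant.

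If the simple regressions are kept instead, call the variables predictors of change, not moderators, and state which arms are included.

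The cost is a change of wording and a few more model terms, with no new data. The downside is low precision: at about 41–53% power for a slope difference of 0.5 SD per SD, a non-significant interaction would not show that moderation is absent.

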### Processing speed training

#### Healthy individuals

Processing speed training has the primary aim of improving mental processing of increasingly complex information that can be processed accurately within briefer periods. The majority of the processing speed training literature in healthy populations focuses on older adults. For example, in a paper analyzing six different studies using a visual information processing speed-training paradigm, the authors found that speed of processing improved among 55 to 95 year olds, and that benefits of training lasted for at least 2 years in some cases [73]. In addition, improvements in processing speed were related to improvements in everyday functioning, including instrumental activities of daily living and driving abilities, providing evidence of far-transfer effects [73]. Importantly, one of the biggest predictors of cognitive gains following processing speed training is pre-training processing speed abilities, such that persons with slower initial speed benefit the most from training [73].

One recent study examined the effects of processing speed training in young, healthy adults [74]. This research group found that processing speed training (using several adaptive training tasks, such as a Visual Number Matching task) led to near-transfer improvements in processing speed in adults with a mean age of 21.6 years, although no evidence of far-transfer was found in measures of fluid intelligence, working memory, or inhibition [74]. Another group found increases in efficiency of attentional resource allocation, as measured by pupil dilation, following processing speed training in young adults [75]. Thus, there are mixed results on near- and far-transfer gains of processing speed training with healthy populations, with evidence suggesting that initial processing speed abilities are an important moderator in treatment outcomes.

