#### Schizophrenia patients

Given that schizophrenia patients have prominent deficits in processing speed and that processing speed has been strongly related to everyday functioning, it logically follows that processing speed training may be an important method of improving functioning in patients. Examinations of processing speed training with schizophrenia patients to date have solely been part of larger programs of cognitive remediation, with several studies finding that broad-based cognitive remediation programs lead to improvements in processing speed in patients [77–80]. Overall, a recent meta-analysis shows a medium-sized effect (*d* = .48) of general cognitive remediation therapy on improving processing speed across a total of 655 schizophrenia patients [4]. However, targeted processing speed training studies with schizophrenia patients are needed to better understand the mechanisms of processing speed enhancement through training in patients. Given that individuals with slower initial speed appear to benefit the most from training, coupled with the fact that schizophrenia patients typically have reduced processing speed abilities (that is, approximately 1 to 2 standard deviations below healthy controls) [81], the current study conceptualizes processing speed training as an active training condition rather than an active control condition for individuals with schizophrenia.

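### The moderator analysis regresses change on a single variable with no arm term, so it cannot separate moderators of training from predictors of retest change, and it would mislead for baseline ability

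*Protocol article*

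**What the plan says.** All references are to the protocol article.

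- **Statistical analysis.** For outcomes that show significant training gains, exploratory simple regressions are to examine potential moderators: "regression analyses will be conducted using individual difference variables (for example, medication usage, sleep quality, duration of illness, intrinsic motivation) as the independent variable". The outcome in each regression is the patient's change score in that domain. The list is introduced as examples, so it is open. No arm term, interaction or use of the control arm is mentioned.
- **Objectives and hypotheses.** The exploratory aim concerns "individual difference variables (that is, sleep quality and intrinsic motivation) on training-related gains". This list is closed and shorter.
- **Processing speed training, Healthy individuals.** The section concludes that there is "evidence suggesting that initial processing speed abilities are an important moderator in treatment outcomes".
- **Processing speed training, Schizophrenia patients.** The argument opens "Given that individuals with slower initial speed appear to benefit the most from training", adds that patients are slow, and concludes that "the current study conceptualizes processing speed training as an active training condition rather than an active control condition for individuals with schizophrenia".
- **Working memory training, Healthy individuals.** Differences in baseline performance, including ceiling effects, are offered as a reason for mixed findings.

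Neither list of moderators names baseline ability. Table 1 shows that the tests making up each trained domain are given before training.

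**The concern.** A moderator of training is a variable across which the difference between trained and untrained patients varies. A regression of change on one variable estimates something else: how change varies with that variable among whichever patients are included. Patients also change between two sittings without training, through practice, regression to the mean and clinical fluctuation. A variable that predicts such change would be reported as a moderator of training even if the same slope appeared in the no-training arm.

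The problem is sharpest for baseline ability, the moderator that the Background stresses. The pre-training score is part of the change score, so predictor and outcome are linked whatever the training does. At stake is a secondary message about who benefits. An unsupported statement that slower patients gain most would also seem to confirm the Background's reasoning about processing speed training.

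**Working it through.** The plan gives no figure to reproduce here. The check asks what the stated model would return under no moderation.

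**Inputs**
- Arm size 27 (Recruitment process and study population); with the 10% dropout allowance, 27 × 0.9 = 24.3, about 24.
- Pre-post correlation r is not given. Range 0.5 to 0.9 assumed.
- Equal pre and post SDs assumed.
- Two-sided 0.05 test assumed for the regression. The share of null trials significant in the negative direction should then be 2.5%.

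**Any moderator Z.** Slope of change on Z in a trained arm = slope in the control arm + moderation. The stated model returns the sum. Only the difference between arms isolates the second term.

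**Z = baseline, no moderation.** With common SD σ:
- Cov(pre, post − pre) = rσ² − σ² = −(1 − r)σ²
- Var(post − pre) = 2(1 − r)σ²
- Slope = r − 1
- Correlation = −(1 − r)/√(2(1 − r)) = −√((1 − r)/2)

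For r = 0.7 the slope is −0.30 and the correlation is −√0.15 = −0.39. Simulation used 20,000 null trials per cell and the same true gain of 0.7 SD for every patient:

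| r | Slope | Correlation | Slope negative, n = 24 | Significant and negative, n = 24 | Significant and negative, n = 27 |
|---|---|---|---|---|---|
| 0.5 | −0.50 | −0.50 | 99.5% | 74% | 78% |
| 0.6 | −0.40 | −0.45 | 98.7% | 61% | 67% |
| 0.7 | −0.30 | −0.39 | 97% | 48% | 53% |
| 0.8 | −0.20 | −0.32 | 94% | 33% | 37% |
| 0.9 | −0.10 | −0.22 | 86% | 18% | 20% |

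**Dependence on equal SDs.** In general the slope is r × SDpost/SDpre − 1. It stays negative while SDpost/SDpre is below 1/r, which is 1.43 at r = 0.7 and 1.11 at r = 0.9.

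**Wrong direction.** Suppose slower patients truly gained less, with the trained arm's pre-post slope 0.1 above the control arm's, and r = 0.7 in controls. The trained change slope is 0.7 + 0.1 − 1 = −0.20, so the simple regression still points to slower patients gaining more. The control slope is −0.30, and the difference, −0.20 − (−0.30) = +0.10, recovers the truth.

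**Baseline by arm.** With 24 trained and 24 control patients, no moderation, and r = 0.5, 0.7, 0.8 and 0.9 (6,000 trials each), the mean interaction estimate was −0.004 to 0.001 and the two-sided type I error 4.9% to 5.1%. With baseline in the model, the interaction is the same whether the outcome is change or the post-training score.

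**Precision of that interaction.** At r = 0.7 the residual SD is √(1 − 0.49) = 0.714. The approximate standard error is 0.714 × √(2/n): 0.21 at n = 24 and 0.19 at n = 27. Power of 80% needs a slope difference of about 2.8 standard errors, or 0.54 to 0.58 SD per SD.

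**The case against.** The strongest reply is that the artefact belongs to an analysis nobody has planned. The named variables (medication, sleep, illness duration, motivation) are not components of the change score, and nothing says that change will be regressed on baseline. This stands: a reader might infer that the plan will produce a false finding about slow starters, and the text does not support that. The percentages describe what would happen if baseline entered through the open list.

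Second, omission from an open, exploratory list in a condensed article is minor. That also stands, taken alone.

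Third, a reader might infer that the premise behind the processing speed arm goes untested. That is too strong. The Background argues largely between populations: slower groups benefit, and patients are slower than healthy people. Whether the training works in patients is tested directly by comparing that arm with control. Baseline moderation within an all-patient sample tests the rationale only in part.

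Fourth, interactions at this sample size will settle little. True, but an imprecise estimate of the right quantity is preferable to a more precise estimate of the wrong one.

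The replies do not touch the stated method. The article fixes a simple regression as its means of examining moderators, and for any variable that regression leaves the control arm's slope out of the comparison.

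**Conclusion.** The concern holds as a weakness in a stated exploratory method. A simple regression of change on one variable, without arm or interaction, cannot identify moderators of the training effect. For baseline ability it would tend to return the Background's expected pattern when no moderation exists: significant in about 18% to 78% of null trials with 24 to 27 patients, against 2.5% in that direction. The range rests on equal pre and post SDs and an assumed r of 0.5 to 0.9, and applies only if baseline is used as a predictor. The expected sign is nearly certain, but significance is not; at r = 0.8 or above it is less likely than not. The effect is confined to exploratory statements about who benefits. The primary between-arm comparisons are unaffected.

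**What to change.** Replace the simple regressions with models for the post-training score that contain its baseline value, arm, the moderator (measured before training) and moderator by arm, contrasting each training arm with control. Include the baseline composite of the trained domain among the moderators, and make the lists in Objectives and hypotheses and in Statistical analysis agree. Report each interaction with its 95% interval, label it exploratory, and state that change will not be regressed on its own baseline.

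The cost is a sentence or two and a few extra models on data already being collected. The downside is imprecision at 24 to 27 per arm: only large slope differences would be detectable, and the result would bear only partly on the between-population rationale.
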